### Sample size

The primary outcome measure, the AQ, has been used for the power calculations. In previous RCTs using the AQ as an outcome measure, effect sizes of 0.79–1.42 [14, 15] were demonstrated. However, as the present intervention will use low-end cardboard VR goggles instead of expensive head-mounted displays, the current study uses a more conservative estimate for the post-treatment effect on the AQ. In order to detect a difference between the experimental and the waitlist control condition with a standardized effect size (Cohen’s d) of 0.50 (two-sided), an alpha of 0.05 and statistical power (1 − *β*) of 0.80, we need 64 participants in each condition (128 participants in total). With an anticipated dropout of 40%, this requires a total target sample size of 180 participants.

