**Methods/design:**

Participants (*N* = 180, aged 18–65 years) with acrophobia symptoms will be recruited from the Dutch general population and randomized to either 0Phobia (*n* = 90) or a waitlist control condition (*n* = 90). 0Phobia will be delivered over a period of 3 weeks and includes psychoeducation, VR exposure, cognitive techniques, monitoring of symptoms, and relapse prevention. The primary outcome measure will be the Acrophobia Questionnaire. Secondary outcome measures will include user-friendliness, symptoms of anxiety, depression, and mastery. Assessments will take place online at baseline, directly after the intervention (post test) and at follow-up (3 months).

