## Methods/design

### Study design

A RCT will be carried out, in which the efficacy and user-friendliness of a self-guided, 3-week, mobile-app-based VR self-guided treatment “0Phobia” will be evaluated. In total, 180 participants from the Dutch general population will be randomized to two conditions: the experimental condition (0Phobia; *n* = 90) and a waitlist condition (*n* = 90). Measures will be taken at baseline and directly after the intervention (post test). After post-test assessment, the waitlist group will be granted access to the intervention. The experimental condition will receive a final follow-up questionnaire 3 months after baseline (follow-up). All measures will be completed online. Two reminders will be send (one by email, one by telephone) if necessary. This study has received ethical approval by the Medical Ethics Committee of the VU University Medical Center (registration number 2016–563) (Trial registration: NTR 6442). Figure 1 presents the flowchart of the study.

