### Randomization, blinding, and treatment allocation

A randomization list will be created with Random Allocation Software using block randomization of 6, 8, 10, and 12 blocks at an allocation ratio 1:1. Participants will be randomized into two groups: experimental or waitlist condition. The randomization list is kept by an independent researcher. This person reveals the next randomization outcome after every inclusion and thus ensures that the researchers are blind for treatment allocation. Due to the nature of the study, it is not possible to blind the participants for the randomization outcome.

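### The target of 180 does not allow for the stated 40% dropout: it leaves 54 per arm and about 73% power at d = 0.50, not 80%

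*Protocol article*

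**What the plan says.** The Sample size section bases the calculation on the post-treatment difference in the Acrophobia Questionnaire (AQ) between 0Phobia and waitlist. The effect is a standardised difference "of 0.50 (two-sided), an alpha of 0.05", with power 0.80, from which the authors conclude that "we need 64 participants in each condition (128 participants in total"). The dropout allowance follows in the next sentence: "With an anticipated dropout of 40%, this requires a total target sample size of 180 participants".

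The number is carried into the design. Under Study design, "In total, 180 participants from the Dutch general population will be randomized to two conditions", with 90 in each, and the section on randomization fixes allocation "at an allocation ratio 1:1". The abstract and the eligibility section repeat 180. No other dropout figure or inflation rule appears in the article.

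**The concern.** The two sentences of the Sample size section cannot both be right. If 40% of 180 participants drop out, 60% of 180 remain, which is 108 and not the 128 said to be needed. The allowance looks like 40% added to the required number, whereas the required number has to be 60% of those randomised.

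The stake is the power claim for the primary outcome. If attrition is what the authors expect, the trial would run with a type II error of about 27% instead of 20% at its own design effect. A null result would then be read as coming from a trial with 80% power, which it would not have had.

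**Working it through.** **Inputs**, all from the protocol article: d = 0.50 (so SD = 1), alpha 0.05 two-sided, power 0.80, 64 per arm (128 in total), dropout 40%, all from Sample size; 1:1 allocation from the randomization section; 180 randomised as 90 + 90 from Study design.

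**Step 1. Evaluable number.** A two-sample t-test with these inputs needs 63.77 per arm, rounded up to 64. Power at 64 per arm is 80.1%. The normal approximation gives 63. The plan's 64 per arm and 128 in total are reproduced.

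**Step 2. Dropout allowance.** To retain n after a proportion q is lost, randomise N = n/(1 − q):

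- 128/(1 − 0.40) = 213.3, so 214, or 107 per arm.
- The stated 180 is 34 fewer (34/214 = 16%).
- 128 × (1 + 0.40) = 179.2, which rounds up to 180.

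The article does not show its step, so multiplication by 1.4 is an inference. It gives exactly 180, and the other variants tried with N = n/(1 − q) do not: starting from the normal-approximation 126 gives 126/0.60 = 210, and a one-sided test (51 per arm) gives 102/0.60 = 170.

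**Step 3. What 180 delivers at 40% dropout.**

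- Remaining: 180 × 0.60 = 108, or 54 per arm, which is 20 short of 128.
- Power for d = 0.50 at 54 per arm: 73.1% (t-test), 73.8% (normal approximation).
- Effect detectable with 80% power at 54 per arm: d = 0.544.

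**Step 4. The dropout that 180 does support.** 1 − 128/180 = 0.289, that is, 52 losses in total.

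**Step 5. Sensitivity to unequal loss.** With the same 108 remaining but split unequally:

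| Evaluable per arm | Power at d = 0.50 |
|---|---|
| 54 and 54 | 73.1% |
| 45 and 63 | 71.9% |
| 36 and 72 | 68.0% |

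**Step 6. Sensitivity to baseline adjustment.** If the analysis adjusts for baseline AQ, the effective standardised difference is 0.50/√(1 − ρ²), where ρ is the baseline to post-test correlation. The article gives no value for ρ, so those below are assumptions.

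| Assumed ρ | Power at 54 per arm |
|---|---|
| 0 | 73.1% |
| 0.3 | 77.0% |
| 0.4 | 80.2% |
| 0.5 | 84.4% |
| 0.6 | 89.6% |

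**The case against.** Four points can be made for leaving the sentence alone.

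- **The design effect is conservative.** The section cites effects of 0.79 to 1.42 in earlier AQ trials and chooses 0.50 as a cautious value. At 54 per arm, power is about 87% for d = 0.60 and 98% for d = 0.79, so the shortfall matters only near the bottom of the plausible range. This stands as context and limits the practical damage. It does not make the claim right, because the power is stated for 0.50, chosen because cheap goggles may work less well.
- **The primary analysis is intention-to-treat and missing outcomes may be imputed.** The Statistical analyses section does say so, but makes imputation depend on the attrition findings. Imputing from baseline scores and background characteristics cannot be assumed to restore the lost information. The sample-size calculation does not invoke it: by inflating for dropout at all, it treats dropouts as lost.
- **Regression on baseline would regain the power.** It could, if ρ is about 0.4 or more. The Sample size section neither claims adjustment nor gives a correlation, so this is a possible repair of the statement and not a defence of it.
- **The 1.4 multiplication is not shown.** True, and it should be described as the likely source only. The error does not depend on it: 60% of 180 is 108, however 180 was obtained.

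**Conclusion.** The concern holds. The evaluable number is right and the dropout allowance is wrong. At the stated 40% dropout, 180 randomised gives about 73% power for d = 0.50, some 7 points below the stated 80%, with 80% reached only at d = 0.544. For the claim as written the target would have to be 214.

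The 73% assumes an unadjusted two-sample comparison of participants with observed outcomes, equal loss in the two arms, and 40% loss at the assessment on which the arms are compared. Unequal loss lowers it; adjustment for a well-correlated baseline raises it. That 180 cannot retain 128 at 40% dropout needs none of these assumptions.

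This is a false statement about power on the primary outcome, not a fatal flaw in the design.

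**What to change.** Recruitment was under way when the article was submitted, so the proportionate change is to keep 180 and correct the sentence in one of two ways:

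- 180 randomised retains the required 128, and so 80% power for d = 0.50, provided dropout does not exceed about 29%; or
- with 40% dropout, 54 per arm remain, giving about 73% power for d = 0.50 and 80% power for d = 0.54 (unadjusted, observed cases, equal dropout).

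If the primary model will adjust for baseline AQ, the authors may add that 80% is regained at 54 per arm when the baseline to post-test correlation is about 0.40 or more. That correlation should be labelled as an assumption and shown with a range, for example 77% power at 0.3 and 84% at 0.5.

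The cost is one corrected sentence, repeated wherever the same claim appears (the registry entry was not available to check), and no further participants. Raising the target to 214 would make the present sentence true, at the cost of 34 more participants.

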### Randomization, blinding, and treatment allocation

A randomization list will be created with Random Allocation Software using block randomization of 6, 8, 10, and 12 blocks at an allocation ratio 1:1. Participants will be randomized into two groups: experimental or waitlist condition. The randomization list is kept by an independent researcher. This person reveals the next randomization outcome after every inclusion and thus ensures that the researchers are blind for treatment allocation. Due to the nature of the study, it is not possible to blind the participants for the randomization outcome.

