### Procedure

Advertisements with a call to participate in a VR mobile app study for acrophobia will be posted on several websites (e.g., proefpersonen.nl, Facebook) and in magazines (e.g., VU magazine). Media coverage in national television and radio broadcasts will provide additional publicity for the study. Potential participants are directed to the study website (http://www.0-phobia.nl) where information about the study is provided including eligibility criteria. Interested participants can leave their contact details at the website. The research team will send them a screening questionnaire to assess eligibility. Ineligible participants will be automatically directed to a screen explaining why they cannot participate in the study. The screening questionnaire assesses level of depression and suicidal thoughts, inclusion and exclusion criteria only. Participants excluded as a result of high levels of depression are advised to contact their general practitioner (GP). In case of high risk for suicide, participants are contacted by telephone by a member of the research team. The participant will be asked for permission to contact their GP.

Eligible participants receive an information letter and consent form with a return envelope. If necessary, they will be reminded by email to complete the informed consent (two reminders in total). After receiving the signed consent form, participants are invited to fill out an online screening battery. After completion, an independent researcher will assign participants to either the experimental condition or the waitlist condition based on the randomization list which is created by using Random Allocation Software. The participants will be send an email stating to which condition they are assigned. Participants assigned to the intervention condition will be sent the VR goggles by postal delivery – along with user instructions for the VR goggles, instructions to conduct the VR sessions (e.g., to start sitting and when anxiety decreases to stand up, to remove sharp objects in their vicinity to avoid injury, to practice each day at a set time), and instructions on how to download and use the 0Phobia app.

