The app is accessed with a unique individual code on the participant’s own smartphone. Once the app is installed, participants can begin with 0Phobia intervention which they can follow for 3 weeks at their own pace. During this 3-week period participants receive weekly motivational emails with information reminding them to start or continue with 0Phobia to increase intervention adherence. These emails will be sent unconditional of app activity.

If participants have questions or experience severe distress, they are encouraged to contact the research team.

After module 6, participants are encouraged to seek out heights in real life. Therefore, participants who finish 0Phobia who have finished module 6 earlier than the 3 weeks will receive an email with a link to the Acrophobia Questionnaire (AQ [28]) in order to obtain estimates of the treatment on levels of acrophobia through VR exposure.

Directly following the conclusion of 0Phobia, participants are sent a link to the online post test. After completing the post test, the waitlist condition will be granted access to the 0Phobia therapy. After 3 months, participants in the experimental condition are asked to fill in the follow-up questionnaire.

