### Data monitoring and management

All data will be collected at the Section Clinical Psychology of VU University of Amsterdam by a staff member and handled confidentially. The data (baseline, AQ after module 6, post test, and follow-up data) will be captured electronically in a secured online survey platform [46]. Through the 0Phobia app the following data is collected: anxiety level during VR exposure, time spent in VR, number of VR sessions completed, and information from three exercises (setting goals for the intervention, evaluating anxiety provoking thoughts and creating a personal fear hierarchy). The data will be coded which serves as a trial identifier consisting of four numbers and captured electronically in a secured online database, which is hosted on a server of our university. No personal identification data will be collected through the app. The data will be uploaded into the IBM SPSS database. Data from the different measurements will be kept in separate databases and merged into a master database only after data collection is completed and each individual database is locked. Data will be coded and the key connecting names to numbers will be kept in a separate, secure location in the principal investigator’s office. The data will be anonymized but linked with the trial identifier consisting of four numbers. Coded data will be electronically stored at the VU Amsterdam, separate from identifying information. Access will be password protected. Only the principal investigators and trial researchers will have access to the final dataset. All collected data will be used only for the purposes of this research. The project group will analyze the data, and both positive and negative trial results will be disclosed. The publication policy is in agreement with the publication statement of the CCMO (see: http://www.ccmo.nl). A data monitoring committee is not required by the Ethics Committee because of the low impact on the safety of the participants. No interim analysis is anticipated as this is not required for a trial of this type.

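### The protocol presents allocation concealment as researcher blinding, and its own support arrangements contradict that blind for staff in contact with app users

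*Protocol article*

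**What the plan says.** Randomization, blinding, and treatment allocation states that "The randomization list is kept by an independent researcher" and that this person "reveals the next randomization outcome after every inclusion and thus ensures that the researchers are blind for treatment allocation". It then says of participants that "it is not possible to blind the participants for the randomization outcome". Procedure agrees on who allocates: once the baseline battery is complete, "an independent researcher will assign participants to either the experimental condition or the waitlist condition based on the randomization list".

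Other sections describe what follows assignment:

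- Procedure: "Participants assigned to the intervention condition will be sent the VR goggles by postal delivery". In the account of the app period it adds: "If participants have questions or experience severe distress, they are encouraged to contact the research team".
- Harms names the research assistant and the principal investigator as contacts for participants who react badly, including while they are using the intervention.
- Study design: "Two reminders will be send (one by email, one by telephone) if necessary". All measures are completed online, and only the experimental arm receives the 3-month follow-up.
- Data monitoring and management: "The project group will analyze the data, and both positive and negative trial results will be disclosed".
- Statistical analyses makes imputation of missing outcomes conditional on what the attrition comparison and the Lee bounds show. It gives subgroups by example only.

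**The concern.** Concealment and blinding protect against different things. Concealment stops knowledge of the next assignment from influencing who is enrolled. Blinding stops knowledge of the actual assignment from influencing what happens after enrolment. The sentence describes a mechanism for the first and claims the second. The next sentence concedes only that participants are unblinded, so a reader assessing bias would conclude that the researchers are masked throughout.

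What is at stake is narrower than in a trial with clinician-rated outcomes. The Acrophobia Questionnaire is filled in online by the participant, so no staff member scores it. Knowledge of arm can still act through how staff deal with participants, how reminders are pursued, and choices made at analysis.

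**Working it through.** The protocol gives no figure on this point and no arithmetic applies. The check sets the sections against each other.

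1. **What the mechanism delivers.** The list is held independently, the holder assigns, and each outcome is disclosed after inclusion. This hides the upcoming assignment until the participant is in the trial. Nothing in it restricts knowledge of the assignment afterwards, so the conclusion drawn in the sentence does not follow.

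2. **Whether another arrangement delivers the blind.** Before the post test, only the experimental arm has the app. Procedure directs participants with questions or severe distress to the research team, and Harms directs those with an adverse emotional reaction during the intervention to the research assistant and the principal investigator. A conversation about difficulty with the app discloses the arm. For these staff the blind is contradicted.

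3. **Other arm-specific steps.** The extra questionnaire link after module 6 (Procedure) and the 3-month follow-up (Study design) go to the experimental arm only. Whoever operates them must know the arm, unless they are automated or run by the independent researcher. The article does not say which.

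4. **Analysis.** The project group analyses the data, and no masked analyst is described. Two choices are left to depend on the data: whether missing outcomes are imputed, and which subgroups are examined. Analysts who know the arms would make both with the direction of the treatment effect in view.

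5. **Reminders.** One email and one telephone reminder are planned, to be used as needed. Neither is restricted to one arm and no caller is named. The number and type are therefore the same on paper, but the article does not say that the procedure is applied identically in both arms.

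6. **Whether an A/B-coded file would mask.** Not if it holds everything. App usage before the post test, the module-6 questionnaire and the 3-month follow-up exist only for the experimental arm. The usability, presence and cybersickness items at post test can be answered meaningfully only by app users. The per-protocol sets also depend on follow-up return or module completion. A file limited to baseline data and the post-test AQ avoids these giveaways.

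**The case against.** The strongest defence is that the sentence means concealment only, that participants are openly declared unblinded, and that no researcher rates the outcome, so this is a slip of terminology with little effect. Weekly emails go out regardless of app activity and so are not discretionary. Attrition is to be examined with a balancing table and Lee bounds, and the separate databases are merged only after each is locked. Call scripts and coded-arm analysis may sit in a fuller document.

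Much of this stands. Unblinded self-report is the larger source of bias, it is disclosed, and correcting this sentence leaves it unchanged. The absence of a call script or masking plan is not itself a fault in an article. But if only concealment is meant, the wording is still wrong and needs the same correction. Separate locked databases do not mask arm once they are merged, and the Lee bounds are one of the results on which the imputation decision depends.

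A reader might infer more than the text supports:

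- *That the research team ships the goggles.* The sentence is passive and names no sender; it could be the independent researcher.
- *That staff telephone, or supply phones to, one arm only.* The telephone reminder is not tied to an arm, and participants use their own smartphones.
- *That later waitlist access breaks the blind.* Access comes after the post test, so it cannot unblind anyone before the primary comparison.
- *That unequal calling would produce a calculable attrition gap.* One could take 40% of 90, which is 90 × 0.40 = 36 per arm, as the pool awaiting a call. But the 40% in Sample size is anticipated dropout and reads more naturally as final loss after reminders. The number outstanding before the call and the proportion recovered by it are not given, and nothing shows that effort would differ by arm.

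**Conclusion.** The statement that researchers are kept blind is wrong as reasoned, because the procedure gives allocation concealment only. It is contradicted for staff who support app users during the intervention. It would go too far to say that no researcher is blind: the article does not say to whom each outcome is revealed, and some roles could remain unaware of arm.

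The consequence is limited to staff contact, reminders and result-dependent analysis choices. Neither its size nor its direction can be obtained from the document. The conclusion rests on one assumption beyond the text: that a participant who contacts staff about the app thereby reveals the arm.

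**What to change.** Replace the sentence with wording such as: *Allocation is concealed until assignment; participants and staff in contact with them are not blind afterwards.* Then state which roles, if any, stay masked and how. This is the necessary correction.

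Three inexpensive steps would protect what can still be protected:

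- State that the same reminder procedure applies to both arms. Giving the caller a list without arm would help little, since the participant can disclose it.
- Run the primary post-test AQ analysis on a file with arm coded A/B, the code being held by the independent researcher who already keeps the list. Leave out app usage, the module-6 AQ, the 3-month follow-up, and the usability, presence and cybersickness items.
- Fix the imputation rule and the subgroups before the code is opened. Doing so before any comparison by coded group is safer still, because a large difference would itself suggest which group is which.

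The cost is a change of wording, a coded variable and a restricted file; no new role is needed. There are two drawbacks. The trial is then described as open-label for contact staff. And Statistical analyses plans to use app-usage data to model missing outcomes, which would reveal the arm, so imputation that uses those data has to wait until after unmasking, as a sensitivity analysis. The per-protocol analyses likewise follow the opening of the code.
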